#### Secondary outcome analysis

In general, for continuous secondary outcomes, we will perform analyses analogous to the analysis of the primary outcome. Otherwise, we will use either the two-sample t-test or Mann-Whitney U test as appropriate. The use of (log) transformations will be considered for time variables since these tend to be skewed. Binary secondary outcomes will be summarised using numbers/percentages and compared, where appropriate, using the χ^2^ test.

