### Randomisation

All eligible and consented participants will be randomised after baseline assessment to one of two arms. Randomisation is performed using Sealed Envelope, an online software application frequently used in clinical trials. Randomisation will use minimisation to ensure balance across study sites and three groupings of surgical procedures: ear, nose and throat, dental and maxillofacial; urology and gynaecology; and general surgery, orthopaedics and other procedures.

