### Primary outcome analysis

We will analyse using an intention-to-treat approach. Our primary analysis will compare mean mYPAS-SF scores at time point 3 (in the anaesthetic room before induction of anaesthesia) between study groups using a mixed-effects regression model with fixed effects for treatment and specialty, and a random effect for centre. All modelling assumptions will be checked, including the assumption of normality for both sets of residuals. If substantial departures from normality occur, then transformations of the outcomes will be considered to achieve normality (of the residuals). Participants who do not contribute any measurements for the primary outcome will be omitted from this analysis.

In addition, the m-YPAS-SF score at other time points will be analysed:

The mean score at time point 2 will be compared.The number of participants with a score >30 in either the standard care and intervention arms at time points 2 and 3 will be tabulated and compared.

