### Sample size calculation

Local validation of the m-YPAS-SF scoring tool was performed at University College London Hospital. A total of 39 patients, requiring a general anaesthetic for day-case surgery, were observed in the anaesthetic room (time point 3). This showed that 67% of participants displayed significant anxiety on the day of surgery—defined as a m-YPAS-SF score of greater than 30, with a mean m-YPAS-SF score of 37.9 in the anaesthetic room (time point 3), similar to recent published literature^30 31^ and our feasibility trial results. These patients would represent the control arm in the RCT.

The original sample size of 304 patients was calculated to detect a 7.5-point difference in m-YPAS-SF scores between the control and intervention arms at the 5% significance level with 90% power. This assumed a common SD of 26, obtained by combining data assessing the results of mYPAS-SF scores of 3798 children.^26^ Use of this SD over the scores seen in the feasibility trial (15.6 and 7.4 in the standard care and intervention group respectively) was chosen to ensure that the study was not underpowered due to any variability in SD between sites. In addition, the sample size calculation was based on a primary analysis that was adjusted for baseline m-YPAS-SF score and assumed a correlation of 0.7 between the baseline and follow-up values. An attrition rate of 15% was also assumed.

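### Binary secondary outcomes get an unadjusted chi-squared test although allocation is minimised on site and specialty; where those factors predict the outcome, the test is conservative and loses some power

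*Protocol article*

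**What the plan says.** All references are to the protocol article; the statistical analysis plan is not shown.

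- Randomisation: "Randomisation will use minimisation to ensure balance across study sites and three groupings of surgical procedures".
- Primary outcome analysis: the primary comparison uses a "mixed-effects regression model with fixed effects for treatment and specialty, and a random effect for centre". Both minimisation factors are therefore in the primary model.
- Secondary outcome analysis, continuous outcomes: "In general, for continuous secondary outcomes, we will perform analyses analogous to the analysis of the primary outcome". The default for these outcomes is thus also adjusted.
- Same section, fallback: "Otherwise, we will use either the two-sample t-test or Mann-Whitney U test as appropriate". The article does not say what triggers it.
- Same section, binary outcomes: "Binary secondary outcomes will be summarised using numbers/percentages and compared, where appropriate, using the" chi-squared test.
- Primary outcome analysis, dichotomised anxiety score: the numbers of children scoring above 30 "at time points 2 and 3 will be tabulated and compared". No test is named.

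Process measures lists, for comparison between arms, premedication, rescue analgesia and antiemetics, and unplanned admissions. Premedication is also the subject of the seventh research question.

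**The concern.** Minimisation makes the arms more alike on site and specialty than chance would. If those factors predict the outcome, the true sampling variance of the treatment difference falls. A Pearson chi-squared test does not know this: it estimates the variance from the pooled proportion, with the between-site and between-specialty variation left in. The standard error is then too large, the actual type I error falls below the nominal level, and power is lost.

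The plan avoids this for the primary outcome and, by default, for continuous secondary outcomes. It gives no reason for treating binary outcomes differently.

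The article itself makes a site effect plausible for premedication. The Comparator section leaves that decision to the individual anaesthetist, and has each site's standard care recorded by questionnaire because it is expected to differ. At stake is some precision on a named research question and on the other binary outcomes. For an outcome that could show harm, such as unplanned admission, a conservative test is not automatically the safe choice.

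**Working it through.** **1. The plan's own figures.** The sample size is powered "at the 5% significance level with 90% power", for a 7.5-point difference with SD 26 and 15% attrition (Sample size calculation). Two-sided testing is assumed.

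- Per arm: 2 × [26 × (1.960 + 1.2816) / 7.5]² = 2 × 11.24² ≈ 252.6, so 253; total 506.
- With attrition: 506 / 0.85 = 595.3, so 596. This matches the revised size.
- With baseline adjustment at correlation 0.7: 252.6 × (1 − 0.49) = 128.8, so 129; total 258; 258 / 0.85 = 303.5, so 304. This matches the first size.

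Both figures reproduce and neither depends on this point. The 506 is used below as the number analysed.

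**2. The mechanism.** Let R² be the share of outcome variance explained by site and specialty. With near-perfect balance, the true variance of the difference is about (1 − R²) times the variance that chi-squared uses. The actual two-sided type I error at nominal 5% is then about 2Φ(−1.96 / √(1 − R²)):

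- R² = 0: 5.0%.
- R² = 0.10: 1.96 / 0.949 = 2.066, giving 3.9%.
- R² = 0.20: 1.96 / 0.894 = 2.191, giving 2.8%.

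These R² values are illustrative. The article gives none.

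**3. Simulation with minimisation.**

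*From the article:* 506 analysed; 1:1 allocation; minimisation on site and three specialty groups; a control rate of 67%, the proportion scoring above 30 in the local validation sample.

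*Assumed:* 15 sites of unequal size; 80% probability of the arm that reduces imbalance; a second control rate of 20%; centre SD on the log-odds scale of 0, 0.43, 0.6 or 1.0, paired with specialty SD of 0, 0.2, 0.4 or 0.6; log odds ratio −0.6 (odds ratio about 0.55) for power.

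The centre intraclass correlation (ICC) is SD² / (SD² + 3.29), giving 0, 0.05, 0.10 and 0.23. Each scenario has 3,000 replicates, so the Monte Carlo standard error is about 0.4 points at 5%: √(0.05 × 0.95 / 3000) = 0.004. The adjusted comparator is a linear model with site and specialty indicators, standing in for the logistic mixed model. Losses come from unrounded values.

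| Control rate | Centre ICC | Type I error, chi-squared / adjusted | Power, chi-squared / adjusted | Power loss (points) |
|---|---|---|---|---|
| 67% | 0 | 4.7% / 4.7% | 90.7% / 90.8% | 0.0 |
| 67% | 0.05 | 4.7% / 5.2% | 88.5% / 89.3% | 0.8 |
| 67% | 0.10 | 3.7% / 4.9% | 85.7% / 87.5% | 1.9 |
| 67% | 0.23 | 2.9% / 5.2% | 77.9% / 84.2% | 6.3 |
| 20% | 0 | 5.1% / 5.0% | 68.1% / 67.7% | −0.4 |
| 20% | 0.05 | 4.7% / 5.1% | 66.8% / 67.7% | 0.9 |
| 20% | 0.10 | 4.0% / 4.7% | 67.0% / 69.5% | 2.5 |
| 20% | 0.23 | 3.1% / 4.9% | 64.4% / 70.9% | 6.5 |

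The simulation agrees with step 2. Adjusting for factors that do not matter costs at most 0.4 points of power.

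**The case against.** The strongest reply is that the error is on the conservative side, is confined to secondary outcomes, and has a size that rests on centre and specialty effects the article does not give. All of that stands, and it limits the weight of the point. It does not remove it: the chi-squared test is a method the article names, not a detail left open, and it departs from the plan's own primary model without a stated reason.

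A reader might infer more than the text supports in five ways.

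- *That all secondary outcomes go unadjusted.* They do not. The mixed model is the default for continuous outcomes; the t and Mann-Whitney tests are an unadjusted fallback.
- *That no effect size will be reported.* Percentages by arm are promised, and an effect measure with its interval is ordinary content for the statistical analysis plan, which is not shown.
- *That the above-30 comparison is a chi-squared test.* The article names no test for it. The binary rule may govern it, but that is an inference.
- *That days of work or school missed will be analysed by a rank test unsuited to the social cost analysis.* Nothing assigns a rank test to that outcome. The fallback also allows a t-test, which compares means, and the costing method is not described.
- *That the loss is large.* A difference of 19 points (51% against 70% power) can be produced, but it takes six equal centres, exact balance within centre and outcome rates running from 2% to 80%. In the same set-up with rates from 10% to 35% the loss is one point (71% against 72%).

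The statistical analysis plan may already specify adjusted binary models. If so, the article's wording is what needs correcting.

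**Conclusion.** The point holds in a limited form. The named test for binary secondary outcomes ignores both minimisation factors, at odds with the primary model and with the default for continuous secondary outcomes. Over the range assumed here, its type I error is about 3% to 5%. Its power is 0 to about 6.5 points below an adjusted analysis, and about 1 to 2.5 points below in the weak-to-moderate scenarios (ICC 0.05 to 0.10). With no site or specialty effect there is no meaningful loss.

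These sizes rest on the assumed number of sites, ICC, specialty effect, treatment effect and 20% rate. The direction rests only on the factors being prognostic, which is plausible for premedication but not shown. There is no inflation of false positives and no effect on the primary result or on the sample size of 596. The change is worth making because it is close to free.

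**What to change.** Make the main analysis of each binary secondary outcome a logistic mixed model that mirrors the primary one: treatment and specialty group fixed, centre random. Report an odds ratio or a standardised risk difference with a 95% confidence interval, and say in advance which. Apply the same rule to the above-30 comparison if it is meant to follow the binary outcomes, and say so.

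Where events are too few for the model to be fitted reliably, use a stratified (Cochran-Mantel-Haenszel) or exact test, with the switching criterion written down beforehand. Chi-squared can stay as a supportive analysis. State also what triggers the t-test or Mann-Whitney fallback, since that is where a continuous outcome would lose its adjustment.

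The cost is a change of wording and a little extra analysis, with site and specialty data already held from allocation. The main risk is non-convergence for rare events, which the fallback covers. The article puts the end of follow-up at May 2024 and does not say whether analysis has begun. The change should be made before arms are compared; if that has already happened, the adjusted results should be presented as additional.

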#### Subgroup analyses

A subgroup analysis will be performed to investigate the effectiveness of the intervention based on the surgical specialty grouping:

Head and neck surgery, dental surgery, maxillofacial surgery.General surgery, orthopaedic surgery, other surgery.Urological surgery, gynaecological surgery.

In addition, a subgroup analysis will be performed to investigate the effectiveness of the intervention according to the age of the patient.

### Other planned analyses

A priori, we will undertake analyses to explore the impact of issues which arose as a result of the COVID-19 pandemic on trial delivery and/or patient characteristics. This will include the following comparisons of participants who were recruited before and after the COVID-19 pandemicBaseline characteristics including parent and child anxiety levels.Time lapsed between randomisation and primary outcome data collection.Compliance with trial protocols including use of the intervention.Subgroup analyses of outcome data.

### Missing data

The proportion of participants missing outcome data will be summarised by treatment arm. The baseline characteristics of those missing follow-up information on the primary outcome will be compared with those with complete follow-up.

We will investigate the impact of missing values in the primary outcome in two ways:

Multiple imputation (using chained equations) may be used to impute missing values of the primary outcome using information collected at other time points. The primary analysis will then be repeated.A mixed model will be fitted that includes outcome data from all time- points.

### Sample size calculation

Local validation of the m-YPAS-SF scoring tool was performed at University College London Hospital. A total of 39 patients, requiring a general anaesthetic for day-case surgery, were observed in the anaesthetic room (time point 3). This showed that 67% of participants displayed significant anxiety on the day of surgery—defined as a m-YPAS-SF score of greater than 30, with a mean m-YPAS-SF score of 37.9 in the anaesthetic room (time point 3), similar to recent published literature^30 31^ and our feasibility trial results. These patients would represent the control arm in the RCT.

The original sample size of 304 patients was calculated to detect a 7.5-point difference in m-YPAS-SF scores between the control and intervention arms at the 5% significance level with 90% power. This assumed a common SD of 26, obtained by combining data assessing the results of mYPAS-SF scores of 3798 children.^26^ Use of this SD over the scores seen in the feasibility trial (15.6 and 7.4 in the standard care and intervention group respectively) was chosen to ensure that the study was not underpowered due to any variability in SD between sites. In addition, the sample size calculation was based on a primary analysis that was adjusted for baseline m-YPAS-SF score and assumed a correlation of 0.7 between the baseline and follow-up values. An attrition rate of 15% was also assumed.

### Interim analysis and revision of sample size estimation and trial protocol

We planned to perform an interim analysis following the recruitment of 100 participants to the trial, to check that the baseline rates and variability in m-YPAS-SF which have guided our sample size calculations hold true in our expanded study population. Due to the pandemic, this was performed early with 119 participants recruited and 67 participants having completed their primary outcome data collection. The primary outcome was analysed with a statistical stopping rule for safety only. This analysis was carried out using a nominal 5% significance level with an O’Brien-Fleming adjustment (within a Lan-de Mets framework). This identified no evidence of harm or need to stop the trial.

However, this analysis revealed a poor correlation between the baseline and preanaesthesia m-YPAS scores. Consequently, the sample size was recalculated without the baseline adjustment, resulting in a revised sample size of 596 patients. The baseline, prerandomisation mY-PAS-SF score was also dropped from data collection.

### Trial start and end dates

The study opened to recruitment in August 2019, and the first patient was recruited and randomised on 19 September 2019. The end date was initially planned to be March 2021; however, the trial was paused between March 2020 and February 2021 because of the COVID-19 pandemic and the cessation of some elective surgical activity and most non-COVID-19-related research activity in the NHS. As described above, the interim analysis which took place in 2020 led to an increase in the planned sample size, which necessitated a further extension to participant recruitment to April 2024; the final participant was recruited on 31 March 2024 and follow-up completed in May 2024.

### Trial management

#### Trial management group

The day-to-day management of the trial is facilitated by a TMG, chaired by the CI which meets a minimum of monthly, and more frequently for cause.

#### Trial steering committee and data monitoring committee

The role of the TSC is to provide independent advice to the TMG and chief investigator, including on approaches to improve the efficiency and feasibility of the trial. The role of the DMC is to provide advice on data and safety aspects of the trial, but where not all members are independent. Meetings of these committees are held approximately once a year, or more frequently if required, to review interim analyses, or as necessary to address any issues. The DMC reviews recruitment and safety data, ensuring appropriate amendments/actions for the trial as necessary.

#### Reporting of adverse events and unintended effects of trial interventions

Expected adverse events related to the use of the VR headset include dizziness, headaches, blurred vision and nausea/vomiting. All other serious adverse events will be reported to the trial management team within five working days of becoming aware of the impact.

#### Patient and public involvement

Patients, carers and the public have been involved throughout the development of the study protocol (including the feasibility study). The PIS, consent form and other patient-facing materials were developed and approved across four National Institute for Health Research (NIHR) Young Persons Advisory Group (YPAG) meetings. There is patient and public involvement representation on the Trial Steering Committee and Trial Management Group, and the TMG Patient and Public Involvement and Engagement representative will contribute to the study report and dissemination of the research findings.

## Ethics and dissemination

The study was approved by the Surrey Borders—Research ethics committee 19/LO/0255, UCL research office as trial sponsor and the Health Research Authority (IRAS 251219) prior to its commencement. The trial is registered with ClinicalTrials.gov NCT03797716 and UCL data protection Z6364106/2018/11/20. All minor and substantial protocol amendments are reported to the sponsor prior to resubmission to the research ethics committee. The study is adopted onto the National Institute of Health Research Portfolio, providing assistance with screening, enrolment, randomisation and data collection (CPMS no: 41142).

The results will be submitted to a peer-reviewed, international journal for publication. Further submissions will be made for secondary outcomes. Dissemination and knowledge mobilisation will be supported by conference attendances, lectures and infographics and engagement with key stakeholders including Royal Colleges, NHS leaders and international colleagues.

## Discussion

Paediatric perioperative anxiety is an important variable that impacts on physiological and psychological outcomes of surgery, as well as having cost implications to hospitals. This study will provide positive or negative high-quality evidence of the effectiveness of a new psychological preparation tool for both parents and children, delivered in the patient’s own home, transforming the way patients are prepared for surgery.

The trial protocol has changed significantly over the course of the study, in part because of the COVID-19 pandemic and consequent changes to paediatric surgical pathways. In particular, the move to remote preoperative assessment in most cases has led to changes in the screening, recruitment and consenting processes, and removal of a baseline, prerandomisation, assessment of anxiety. This measure was initially included for analytic purposes, based on an assumed high correlation with the primary outcome. However, our interim analysis indicated that this correlation was low, and therefore, that the measure was not necessary; as such, the measure was dropped (which assisted in trial delivery, as a face-to-face visit at the time of consent and randomisation was no longer necessary) but the sample size was increased substantially from 304 to 596, including a 15% attrition rate. The post-COVID-19 pandemic changes to healthcare delivery also mean that patients are being offered surgery with much shorter notice than prepandemic. This has led us to reduce the minimum time allowable between randomisation and date of surgery, sequentially over the course of the study, from 4 weeks at the start to 9 days by the end.

The trial has met significant delivery challenges as a result of the COVID-19 pandemic and its consequences; these will be explored further through surveys undertaken with local principal investigators and research staff.
